## Abstract

**Background:**

Working in an operating room (OR) is physically and mentally challenging: the operation itself demands the surgeon's full attention, while time and cost efficiency constraints, daily planning, and emergency care interfere with the procedure. Thus, multitasking becomes an integral surgical competence. This study aims to examine the effect of disruptions during surgery in a highly immersive virtual reality (IVR) operation environment combined with a virtual reality (VR) laparoscopy simulator.

**Objective:**

This study aims to identify distractions in the OR and their importance in the clinical setting.

**Methods:**

An IVR environment was created using a high-resolution, stereoscopic 360° video of the OR. Different distractions were identified, classified as auditory, visual, or audio-visual, and recorded accordingly. The surrounding was combined with a VR laparoscopic simulator. Participants—medical students and surgical residents—received proficiency-based training in basic laparoscopic skills and were blinded to the aim of the experiment. Following a cross-over design, each participant received a unique order of virtual distraction factors while performing tasks on the laparoscopic simulator. During the experiment, subjective passing of time, stress, heart rate, and visually induced motion sickness are recorded. After the experiment, validated questionnaires for usability, immersion, and stress were completed, as well as subjective evaluation of the distractions. The questionnaires used included the system usability scale, Self-Assessment Manikin score, National Aeronautics and Space Administration Task Load Index, and the immersion rating scale as described by Nichols. Performance in the laparoscopic tasks in relation to distractions will be evaluated by the Wilcoxon test and ANOVA for continuous variables. Subgroup analyses in regard to age, gender, and expertise (medical students vs surgical residents) are planned.

**Results:**

The described trial started in August 2022 and is ongoing. By July 2024, a total of 30 medical students and 9 surgeons have completed the study.

**Conclusions:**

We present a study protocol aiming to identify the impact of different disruptions in OR during laparoscopic training in IVR. Hence, it may lead to an improved awareness of distractions and facilitate accommodations toward an improved work environment. Prior research leads to the hypothesis that the performance of a more experienced surgeon is less impacted by distractions than the performance of inexperienced surgeons and medical students. Furthermore, we investigate which type of distraction has the largest impact on performance. With this knowledge, specific multitasking training can be devised, which may be particularly useful in medical education, for which VR might play a leading role. Additionally, workplace surroundings in the OR can be optimized with this knowledge.

**Trial Registration:**

German Registry for Clinical Trials DRKS00030033; https://drks.de/search/en/trial/DRKS00030033

**International Registered Report Identifier (IRRID):**

DERR1-10.2196/59014

## Introduction

Laparoscopic simulation has been shown to be beneficial in the training of surgical residents [1-3] and has been a mandatory part of surgical education in different countries. Following this example, an obligatory laparoscopic simulation curriculum consisting of 6 tasks was implemented in the Department of General, Visceral and Transplant Surgery, University Medical Center Mainz, Germany.

Surgery requires different professions to cooperate closely and efficiently to facilitate a smooth workflow while maintaining high levels of concentration on the procedure itself. Patient safety and cost efficiency demand swift procedures, which are regularly impaired or interrupted by various factors: emergency care, organizational tasks, and management of complications cannot be postponed in many cases; thus, multitasking becomes a surgical key competence. Moreover, teaching residents and medical students remains an integral part of working in an operating room (OR). In combination, these circumstances turn the OR into a bustling workplace with high physical and mental demands, rendering the ability to multitask a key surgical competence. Prior studies have identified and quantified distractions in the OR and examined their influence on surgeons [4-6]. Experienced surgeons were found to be more adept at handling distractions and were less impaired by them [7], suggesting this to be an ability that can be trained.

Laparoscopic simulation training usually takes place away from the hustle of everyday clinical work, yet structured training for multitasking or stress resilience has not been developed so far.

To test laparoscopic simulation in more realistic conditions, the institute designed a highly immersive virtual reality (IVR) application using high-resolution, stereoscopic 360° videos of the OR and displaying them on a head-mounted display (HMD; Vive Pro, HTC Corp) [8,9]. This application includes the surgery-unrelated background work in the OR including typical background noises and movements. In a prior study of our group, an IVR setting using 360° videos was deemed more realistic and was preferred by participants over an artificial virtual reality (VR) setting [10]. Furthermore, it has been previously shown that 360° video-based VR experiences enhanced memory recall, compared to conventional 2D videos [11], suggesting facilitated learning.

Prior studies could show that training in immersive laparoscopy induces a higher cognitive load, making this method already more demanding than conventional laparoscopy training [12]. Sankaranarayanan et al [13] have presented a simulated IVR program with similar goals and were able to show a significant difference in performance with or without distraction. As mentioned, our group was able to show in the past that IVR using real video material is preferred by users over simulated environments [10,14]. We aimed to create a realistic environment with realistic distractions, that is, phone calls or presentations of the next case, in contrast, other studies in the past have used unrelated distractions like music or other noises [13]. To achieve a realistic environment, different distractions were identified and classified as auditory (ie, a phone call), visual (ie, somebody walking through the field of vision), and audio-visual (ie, somebody presenting an emergency case including a computed tomography scan). These distractions were recorded and can be inserted into the simulation at any time. Participants can immerse themselves into this realistic environment and perform tasks on a laparoscopic simulator including haptic feedback (LapSim, Surgical Science, software version LapSim 2020.2). The simulator detects numerous parameters such as task completion time, tissue handling, amount of bimanual work, and instrument path length to calculate a performance score. Laparoscopy tasks are designed to train numerous abilities and competencies.

We present a protocol for a study aiming to identify the impact of different distractions during laparoscopic simulation in IVR. This study aims to identify distractions in the OR and their importance in the clinical setting.

## Methods

### Aims

This study aims to examine the influence of distractions on laparoscopic surgery in IVR. Therefore, a unique presentation sequence was created for each participant repeating the 6 tasks combined with 5 different distractions and without distractions. Each task will be performed with each distraction once and without distraction twice following a cross-over design. Figure 1 depicts one of the distractions in VR.

**Figure 1 figure1:**
[figure not shown]
Part of the participant’s view in immersive virtual reality is shown. The scrub nurse is standing beside the participant. On the left edge of the picture, the laparoscopy monitor with an exercise is shown. In the background, a colleague is demonstrating a CT scan of the next emergency patient with a bowel obstruction (audio-visual distraction). CT: computed tomography.

After completing the proficiency-based curriculum and passing the final tests, all surgical residents as well as residents in gynecology are eligible to participate in the study. As a second group, medical students, who complete the same curriculum with lower thresholds, are eligible to participate in the study. These thresholds were introduced to eliminate the influence of the learning curve during the experiment.

Participants are blinded toward the aim of the study. They are instructed to test the familiar curriculum in an IVR environment but are unaware of possible distractions. Prior research has shown simulation to be a useful tool not only for training practical skills, but also regarding communication, stress, and handling of difficult situations [15].

The results may suggest how to improve the work environment in the OR by identifying distractions, and classifying and reducing them, wherever possible. As mentioned earlier, however, complete elimination is nearly impossible, but reduction should be attempted especially during critical steps of the operation. Different surgeons react differently to stress and distractions [16] and experienced surgeons appear to be less impaired by them [7]. This suggests that the individual reaction to stress may be a subject to training, which could be conducted in VR.

### Objectives

The primary objective of this study is to examine the influence of simulated distractions in IVR on performance in laparoscopic surgery. The LapSim with haptic feedback is able to evaluate laparoscopic performance using the time required for an exercise, tissue handling, amount of bimanual work, and instrument path length. Secondary objectives are to collect participant-specific data, such as grade of immersion, subjective perception of the passing of time, subjective perception of stress in the form of the National Aeronautics and Space Administration Task Load Index (NASA TLX) questionnaire, system usability scale, visually induced motion sickness (VIMS), eye strain, heart rate, and eye tracking behavior.

### Trial Design

The trial is designed as a cross-over trial. Each participant trains in 6 exercises on the simulator until a proficiency cutoff level is reached. After the training phase, participants enroll in the experiment. They complete the exercises wearing an HMD in IVR in a 360° video of the OR while 5 different auditory, visual, and audio-visual distractions are played. Each exercise is completed once combined with all 5 distractions and twice without distractions, amounting to 42 exercises in total. The order of exercises and distractions is determined by a Latin squares design, which minimizes potential order effects as each participant has an individual order of exercises and distractions [17]. The sequences are prepared with control for neighboring exercises and distractions, ensuring that there is no clustering of the same exercises or distractions.

### Study Setting

The study will be conducted as a single-center study in the University Medical Center Mainz, Germany. The Department of General Visceral and Transplant Surgery is a high-volume center for minimally invasive surgery and has implemented mandatory laparoscopy training for all residents. Facilities for training are available. The department conducts mandatory laparoscopy training for all medical students and offers an elective about minimally invasive surgery.

### Eligibility

#### Overview

Eligible are volunteer medical students of the University Medical Center Mainz, who have completed the training of the 6 laparoscopic exercises to a predetermined proficiency level as well as residents in visceral surgery and gynecology after completion of the department-specific laparoscopy training.

#### Inclusion and Exclusion Criteria

Since the presented program is a novelty design there is no effect size known. Due to prior experience, a sample size of 30 medical students and 20 residents in visceral surgery and gynecology was chosen. Medical students are recruited through announcements via posters and flyers in the University Medical Center Mainz, as well as during classes in visceral surgery. Surgical and gynecological residents are informed about the study on a personal basis and recruited if interested. To improve adherence to the experiment, breaks are offered after each exercise and can be taken at the liberty of the participants. The experiment can be paused or discontinued at any time if the participant wishes to, the number and duration of additional pauses will be recorded.

Exclusion criteria are impacted sight or hearing, which are tested before inclusion using standardized tests. All participants must be able to stand for 120 minutes upright to work on the laparoscopy simulator and are excluded if this is not possible. Furthermore, all participants have to complete a laparoscopy curriculum and reach a threshold to rule out the learning curve as an effect on the study. Not passing the threshold is an exclusion criterion.

### Data Collection and Management

Data are collected immediately after the experiment using LimeSurvey (LimeSurvey GmbH, licensed by the Johannes Gutenberg-University Mainz) and later transferred to SPSS (version 27; IBM Corp).

Data are checked manually for correct transfer. Data are going to be stored in anonymized fashion on password-protected computers of the study group in locked rooms, to which only members of the study group have access to.

### Ethical Considerations

The trial including all information, and the consent form has been reviewed and approved by the local ethics committee (Ethik-Kommission der Landesärztekammer Rheinland-Pfalz, application: 2022-16528-andere Forschung erstvotierend). Each eligible participant will be informed concisely about the study's potential and risks. If participation is desired, written consent is obtained by a member of the study group before inclusion in the trial. All participants have the option to withdraw their consent or quit the study at any time. All data is handled confidentially and in an anonymized fashion. There is no compensation for participants.

### Interventions

Performance in laparoscopic exercises will be evaluated with and without different distractions. A cross-over design was chosen to allow within-subject control for each participant. Primary comparators are performance in laparoscopic surgery during different distractions. This will be assessed by the parameters of the laparoscopic simulator. Prior studies have shown more experienced surgeons to be less impacted by distractions [7], deeming the 2 eligible groups—medical students and surgical residents—an interesting contrast. Further comparators are subjective passing of time, subjective stress levels, and heart rate [18-20], as well as usability, VIMS, eye strain, and immersion, which are key comparators in newly developed VR programming [21-23]. Furthermore, the Self-Assessment Manikin score is assessed to employ a measurement for psychological stress and emotion [24]. Most of the aforementioned parameters are assessed by validated questionnaires, which have been used in similar experiments for years. Eye tracking is performed using HMD, to examine whether participants look at distractions without consciously perceiving them.

Each participant is going to complete each of the 6 laparoscopic exercises with all 5 distractions and twice without distraction. This amounts to 42 exercises, breaks will be taken after exercises 14 and 28. Mandatory breaks are 10 minutes long but can be extended as needed. Additional breaks will be offered after each exercise and can be taken at the freedom of the participant. The order of exercises and distractions is determined by a Latin squares design. After each exercise, participants are asked for their subjective stress levels using the NASA TLX score, subjective passage of time, VIMS (measured by the Fast Motion Sickness Scale [17]), and eye strain. After the experiment, participants are questioned about usability and immersion and are asked if they have noticed any distractions and, if yes, of which kind and how disruptive they were perceived to be. The trial design is depicted schematically in Figure 2 with all data collected at different time points.

**Figure 2 figure2:**
[figure not shown]
The course of the study with its different phases and the data collected at different time points. Before enrolling in the study, participants complete a mandatory laparoscopy curriculum. Right before the experiment, a warm-up phase is conducted. During the experiment, data about performance on the laparoscopy simulator as well as heart rate and the items of multiple questionnaires are collected. After completion of the experiment participants evaluate the distractions as well as usability of the system. *NASA TLX: National Aeronautics and Space Administration Task Load Index. **FMS: Fast Motion Sickness Scale. ***SAM: Self-Assessment Manikin. ****SUS: system usability scale.

### Statistical Methods

Statistical analysis of the primary outcome, perceived passage of time, and perceived stress will be conducted using the Wilcoxon test since it consists of a connected sample. Participant-related data, usability, immersion, and visually induced motion sickness are analyzed using repeated-measures ANOVA and 1-tailed *t* tests. Eye tracking is analyzed qualitatively (ie, the participant looked away from the laparoscopy monitor: yes or no). The students’ and residents’ performance, subjective passing of time, and NASA TLX variance over different time points and exercises will be analyzed using ANOVA.

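### The stated eye-tracking variable, gaze leaving the monitor, is only a loose proxy for looking at a distraction without perceiving it

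*Protocol article*

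**What the plan says.** The protocol article lists eye tracking last among its secondary objectives (Objectives): "visually induced motion sickness (VIMS), eye strain, heart rate, and eye tracking behavior".

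Interventions gives its purpose: "Eye tracking is performed using HMD, to examine whether participants look at distractions without consciously perceiving them".

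Statistical Methods gives the variable: "Eye tracking is analyzed qualitatively (ie, the participant looked away from the laparoscopy monitor: yes or no".

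Conscious perception is measured separately. After the experiment, participants "are asked if they have noticed any distractions and, if yes, of which kind and how disruptive they were perceived to be" (Interventions).

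The design also contains undistracted runs (Trial Design): "Each exercise is completed once combined with all 5 distractions and twice without distractions, amounting to 42 exercises in total".

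**The concern.** The aim joins two facts about a distraction: gaze went to it, and the participant was not aware of it. The stated variable captures neither directly. It records that gaze left the monitor, not where it went, and by itself it says nothing about awareness.

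This is more than a detail left out of a short article. The article chose to state a variable, and that variable fits its own question badly. If it is analyzed as stated, ordinary looking around the virtual operating room is counted together with looks at distractions. A high yes rate could then be reported as unconscious attention to distractions when part of it has nothing to do with them.

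**Working it through.** No figure in the plan can be reproduced here, because the article gives no look-away rate and no target for this outcome. The check sets the statements side by side and then shows how far the proxy could err.

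**1. What else can produce a yes.** The Introduction says of the virtual scene: "This application includes the surgery-unrelated background work in the OR including typical background noises and movements". The caption of Figure 1 adds: "The scrub nurse is standing beside the participant". These belong to the scene whether or not a distraction is playing, so off-monitor gaze is possible in undistracted runs too.

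**2. What a yes can mean for each type of distraction.** The Introduction reports that "different distractions were identified and classified as auditory (ie, a phone call), visual (ie, somebody walking through the field of vision"; the third class is audio-visual. For a visual or audio-visual distraction located off the monitor, a no rules out a look at it, but a yes does not establish one. For a purely auditory distraction there may be no object to look at, so a yes has no clear meaning for the stated aim.

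**3. What the design offers.** Per participant:

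- runs with a distraction: 6 × 5 = 30
- runs without: 6 × 2 = 12
- total: 30 + 12 = 42, which agrees with the article.

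Every exercise therefore has two undistracted runs by the same participant. Each distraction is met six times, once per exercise. Noticing is asked once, after all 42 runs. Gaze and noticing can thus be matched by participant and kind of distraction, but not run by run.

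**4. Illustration of the misclassification (all rates assumed).** Suppose gaze is scored once per run. Let *g* be the share of distracted runs with a glance at the distraction. Let *b* be the share of runs with a look elsewhere off the monitor, equal with and without distraction and independent of *g*. Then

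- P(yes, distracted run) = *g* + (1 − *g*)*b*
- share of yes runs with no glance at the distraction = (1 − *g*)*b* / [*g* + (1 − *g*)*b*].

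With *g* = 0.40:

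| *b* | P(yes) | Share of yes runs without a glance |
|---|---|---|
| 0.05 | 0.40 + 0.03 = 0.43 | 0.03/0.43 = 7% |
| 0.10 | 0.40 + 0.06 = 0.46 | 0.06/0.46 = 13% |
| 0.20 | 0.40 + 0.12 = 0.52 | 0.12/0.52 = 23% |
| 0.60 | 0.40 + 0.36 = 0.76 | 0.36/0.76 = 47% |
| 0.90 | 0.40 + 0.54 = 0.94 | 0.54/0.94 = 57% |

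**5. What the undistracted runs recover.** Under the same assumptions, P(yes, undistracted run) = *b*, so the difference is *g*(1 − *b*). At *b* = 0.60 this is 0.76 − 0.60 = 0.16, and 0.16/(1 − 0.60) = 0.40 returns *g*. Even the crude variable gives an indirect answer on gaze once it is compared with the undistracted runs.

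**The case against.** The strongest reply is that everything needed is in the design: gaze is tracked, perception is asked about by kind of distraction, and 12 of 42 runs are undistracted. A reader might infer that the eye-tracking question cannot be answered at all. The documents do not support that, since an indirect answer by participant and kind of distraction is available.

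A second reply is that the parenthesis may only illustrate a qualitative review. The Introduction uses the same abbreviation to give one instance for each of three classes, although there are five distractions. That is fair. Even so, this is the only gaze variable the article names, and as an illustration it still points away from the stated aim.

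Third, the baseline comparison and the link to the noticing question may well be set out in the full protocol or analysis plan. Their absence from an article is not a fault in itself, and the point does not rest on it. Nor does the text say that a look away counts at any moment of a run, or that the participant can see the instruments off the monitor; neither should be read into it.

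Fourth, participants have trained to proficiency, so background look-away could be rare, and the misclassification would then sit at the low end of the table. Nothing in the documents settles this either way.

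**Conclusion.** The point holds as a mismatch between a stated measure and its stated purpose. Gaze leaving the monitor is a loose proxy for looking at a distraction: it also counts looks at the nurse or the moving background, and it may have no visual target when the distraction is only heard.

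It does not follow that the question is beyond the study's reach, or that any particular share of yes scores is wrong. The 7% to 57% range rests on an assumed 40% glance rate, independence and scoring per run. It shows the mechanism and is not an estimate.

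The consequence is limited to a secondary outcome in a study that describes its aim as exploratory. The primary performance outcome is not affected.

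**What to change.** For visual and audio-visual distractions, define the variable as whether gaze fell on the distraction's location while it played (yes or no). As the baseline, score the same location over an equivalent time window in the same participant's two no-distraction runs of that exercise. Then cross-tabulate the result with the noticed or not-noticed answer by participant and kind of distraction, and state that run-by-run matching is not possible because noticing is asked once. Purely auditory distractions should be left out of this analysis or reported separately as look-away only.

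This needs time-stamped gaze targets, and the article does not say whether they were stored. If they were not, compare look-away between distracted and no-distraction runs by kind of distraction, and restate the aim in Interventions as whether gaze left the monitor.

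The cost is modest analysis time in the first case, and a change of wording plus one simple comparison in the second. Neither needs a new measurement. The article reports recruitment as still open in July 2024, so on that account the definition could be settled before the final analysis.

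### The expertise hypothesis is a group-by-distraction contrast, but no named analysis matches it: the student-resident ANOVA names time points and exercises, not distraction

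*Protocol article*

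**What the plan says.** All references are to the protocol article.

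- **Hypothesis.** The Abstract (Conclusions) takes from prior research that "the performance of a more experienced surgeon is less impacted by distractions than the performance of inexperienced surgeons and medical students". The Interventions section gives the same reason for having two groups and calls them "medical students and surgical residents—an interesting contrast".
- **Primary analysis.** Statistical Methods says the analysis of the primary outcome "will be conducted using the Wilcoxon test since it consists of a connected sample". This is a paired, within-person test with no group factor.
- **Student-resident analysis.** The last sentence of Statistical Methods covers the two groups' performance, "subjective passing of time, and NASA TLX variance over different time points and exercises will be analyzed using ANOVA".
- **Abstract, Methods.** "Performance in the laparoscopic tasks in relation to distractions will be evaluated by the Wilcoxon test and ANOVA for continuous variables". It then adds: "Subgroup analyses in regard to age, gender, and expertise (medical students vs surgical residents) are planned".
- **Status.** The Objectives section states: "The primary objective of this study is to examine the influence of simulated distractions in IVR on performance in laparoscopic surgery". No expertise comparison is among the primary or secondary objectives, and the Discussion calls the aim exploratory.
- **Groups.** Under Inclusion and Exclusion Criteria, "a sample size of 30 medical students and 20 residents in visceral surgery and gynecology was chosen". Results reports 30 students and 9 surgeons by July 2024, with recruitment still open. The Aims section says students pass the same curriculum at lower thresholds than residents.

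**The concern.** Being less impacted is a statement about change. The relevant quantity is (distracted minus undistracted) in students compared with (distracted minus undistracted) in residents. An ANOVA of the two groups over time points and exercises, taken as worded, answers other questions: whether one group performs better overall, and how both develop over the session. Separate tests within each expertise subgroup do not answer it either, because a difference between two p values is not a test of the difference between two effects.

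Both routes lean towards the expected answer. Residents have trained to a higher standard, so an overall advantage is likely even if distractions affect everyone alike. The resident group is also smaller, so it is less likely to reach significance for the same true effect. Either result could be read as residents coping better with distraction. The article sees such findings as a basis for targeted multitasking training.

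**Working it through.** **1. What the documents fix.** The sample size has no stated alpha, power, effect size or SD, so there is no power figure to reproduce. The counts agree: 30 + 20 = 50 participants, and 6 × (5 + 2) = 42 runs per person.

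**2. Hypothesis against named analyses.**

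| Analysis | Group named? | Distraction named? | Tests the difference in impact? |
|---|---|---|---|
| Wilcoxon test, primary outcome | no | within person | no |
| ANOVA, last sentence of Statistical Methods | yes | no | not as worded |
| Wilcoxon and ANOVA, Abstract | no | yes | no |
| Expertise subgroup analysis, Abstract | yes | not stated | unclear |

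**3. Separate subgroup tests.** Assumptions: normal individual effects, the same true standardised effect d in both groups, and a two-sided Wilcoxon test at 0.05 in each group. The power values are simulated. P(students significant, residents not) = power(30) × [1 − power(n residents)].

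| d | Power n=30 | n=20 | n=9 | Students only, 30 v 20 | Students only, 30 v 9 |
|---|---|---|---|---|---|
| 0.3 | 0.340 | 0.240 | 0.100 | 26% | 31% |
| 0.5 | 0.732 | 0.543 | 0.220 | 33% | 57% |
| 0.6 | 0.875 | 0.691 | 0.305 | 27% | 61% |
| 0.8 | 0.985 | 0.909 | 0.488 | 9% | 50% |

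Example: 0.732 × (1 − 0.543) = 0.33. The reverse pattern (residents only) is rarer: at d = 0.5, 0.543 × (1 − 0.732) = 15% at 30 v 20, and 0.220 × 0.268 = 6% at 30 v 9. A direct two-sided 5% test of the group difference would wrongly favour residents in 2.5%.

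**4. Overall group difference.** Assumptions: mean run time 100 s in students and 80 s in residents, between-person SD 0.20 and run SD 0.25 on the log scale, and the same percentage slowing in both groups.

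- Log difference: ln(100/80) = 0.223.
- SD of a person's mean: √(0.20² + 0.25²/42) = 0.204.
- At 30 v 20: SE = 0.204 × √(1/30 + 1/20) = 0.059, so z = 3.79 and power is about Φ(3.79 − 1.96) = 97%.
- Simulation with a Welch test gives about 96% at 30 v 20 and 75% at 30 v 9. With students at 160 s both are about 100%.

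The true difference in relative impact is zero throughout.

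**5. Scale.** If both groups slow by 20%, students go from 100 to 120 s (+20 s) and residents from 80 to 96 s (+16 s). The raw changes differ by 4 s from baseline alone, while the log change is ln 1.2 = 0.182 in both. Under the assumptions of step 4, with students at 100 to 160 s and slowing of 10 to 30%, a comparison of raw differences wrongly favours residents in about 13-100% of trials at 30 v 20, and from about 10% to nearly 100% at 30 v 9. The log-scale comparison does so in about 2-3%.

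**6. Precision of the right contrast.** Assuming two-sided alpha 0.05 and 80% power, the detectable group difference, in SDs of the individual change, is (1.960 + 0.842) × √(1/30 + 1/20) = 0.81. At 30 v 9 it is 2.802 × √(1/30 + 1/9) = 1.06.

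**The case against.** A reader might infer that no analysis of the hypothesis is planned and that it will never be tested. The documents do not support that. The Abstract ties ANOVA to performance under distraction and then sets students against residents. That may be meant as a direct comparison, and nothing says that subgroup analysis means separate tests. The article also uses the word exercise for both the 6 tasks and the 42 runs. In the second sense the ANOVA could include the distraction conditions. Model terms are often left to a full protocol or SAP, which is not shown here.

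Further, expertise is not a listed objective and the aim is exploratory, so the primary result is not at risk. No run time, SD or effect size is given, so every magnitude above is assumed. The 30 v 9 split is an interim count. Nothing says the authors would read a main effect as differential impact.

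All of this stands and limits the claim. It does not remove it. The article does name factors for the student-resident analysis, and they are not the ones its hypothesis needs. The Abstract and Statistical Methods also describe the analysis differently. An exploratory estimate must still be of the right quantity.

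**Conclusion.** The point holds as a mismatch between hypothesis and named analysis: the expertise hypothesis concerns group by distraction, and no analysis is described in those terms. The risk is misreading. If separate subgroup tests were used, equal true effects of 0.3 to 0.8 SD would give the hypothesised pattern in roughly 9-33% of trials at 30 v 20 and 30-60% at 30 v 9. An overall group difference would probably be significant whenever residents are clearly faster at baseline. These sizes rest on assumed effects, SDs and run times; the mismatch itself rests only on the text. The comparison of distracted with undistracted performance, which is the primary objective, is unaffected.

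**What to change.** Amend the last sentence of Statistical Methods and bring the Abstract into line:

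- Add distraction as a factor. Name the group-by-distraction term (distracted v undistracted) of a mixed model with participant as random effect. Let the distraction effect vary between participants, so that the test uses the between-person spread.
- Equivalently, take each participant's distracted-versus-undistracted change within exercise, average it over the 6 exercises, and compare that one value between groups.
- Report it two-sided with a 95% CI, and state that it alone supports any claim that residents are less impacted. Overall group differences and separate subgroup p values do not.
- Specify log or relative change for run time and path length.
- Label the contrast exploratory.

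The cost is a few lines of text. The 42 runs per person already supply the data, and recruitment was still open at the last report. The downside is limited precision: 80% power only for a group difference of about 0.8 SD at 30 v 20, so a wide interval should be expected and reported as such.
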